## Abstract

**Background:**

Neuropsychiatric symptoms (NPS) are very common in patients with mild cognitive impairment (MCI) and Alzheimer’s disease (AD) dementia and are associated with various disadvantageous clinical outcomes including a negative impact on quality of life, caregiver burden, and accelerated disease progression. Despite growing evidence of the efficacy of (non)pharmacological interventions to reduce these symptoms, NPS remain underrecognized and undertreated in memory clinics. The BEhavioural symptoms in Alzheimer’s disease Towards early Identification and Treatment (BEAT-IT) study is developed to (1) investigate the neurobiological etiology of NPS in AD and (2) study the effectiveness of the Describe, Investigate, Create, Evaluate (DICE) approach to structure and standardize the current care of NPS in AD. By means of the DICE method, we aim to improve the quality of life of AD patients with NPS and their caregivers who visit the memory clinic. This paper describes the protocol for the intervention study that incorporates the latter aim.

**Methods:**

We aim to enroll a total of 150 community-dwelling patients with MCI or AD and their caregivers in two waves. First, we will recruit a control group who will receive care as usual. Next, the second wave of participants will undergo the DICE method. This approach consists of the following steps: (1) describe the context in which NPS occur, (2) investigate the possible causes, (3) create and implement a treatment plan, and (4) evaluate whether these interventions are effective. Primary outcomes are the quality of life of patients and their caregivers. Secondary outcomes include NPS change, caregiver burden, caregivers’ confidence managing NPS, psychotropic medication use, the experiences of patients and caregivers who underwent the DICE method, and the cost-effectiveness of the intervention.

**Conclusions:**

This paper describes the protocol of an intervention study that is part of the BEAT-IT study and aims to improve current recognition and treatment of NPS in AD by structuring and standardizing the detection and treatment of NPS in AD using the DICE approach.

**Trial registration:**

The trial was registered on the Netherlands Trial Registry (NTR7459); registered 6 September 2018.

## Introduction

### Background and rationale

The majority of patients with Alzheimer’s disease (AD) experience neuropsychiatric symptoms (NPS) during the course of their disease [1, 2]. NPS include behaviors such as apathy, agitation, and psychosis, and are already highly prevalent in patients in the early stages of AD including those with mild cognitive impairment (MCI) [3]. NPS have a large impact on the quality of life (QoL) of patients and their caregivers [4], leading to extensive healthcare costs [5]. In addition, NPS are related to accelerated progression of the disease and earlier institutionalization [6, 7].

Although NPS are increasingly recognized as core features of AD [2], NPS are currently underrecognized during the diagnostic phase in memory clinics. This notion arises from our local experience, but one that has also been raised previously by several international research groups [8–12]. While cognitive testing and instrumental activities of daily living (IADL) questionnaires are typically administered during standard clinical work-up, assessment of NPS (e.g., using the Neuropsychiatric Inventory (NPI)) is often not [13]. The failure of clinicians to prioritize the assessment of NPS leads to undertreatment and a variety of associated suboptimal outcomes [14, 15]. This is clearly a missed opportunity since there is growing evidence for the efficacy of psychosocial and pharmacological interventions to reduce NPS and improve QoL in patients with AD [16–19].

NPS are often considered as medication targets in cases where NPS are appropriately detected by clinicians [11]. This leads to high rates of (off-label) psychotropic medication prescriptions that are only modestly effective in dementia [20]. In addition, this symptomatic treatment does not do justice to the multiple contributors causing NPS, including factors relating to the patient (e.g., personality), caregiver (e.g., communication style), and environment (e.g., safety) [11, 21, 22]. Therefore, a patient-centered care (PCC) approach is preferred that considers all these individual factors when managing NPS [1, 17, 23].

After a comprehensive assessment of NPS, nonpharmacological interventions are the first choice to treat NPS in dementia as recommended by the national and international guidelines on the diagnosis and treatment of dementia [24–26]. Although several psychosocial interventions have been developed and proven to be effective (e.g., [27–29]), these programs have rarely been implemented into standard care in memory clinics [10]. Previous studies have suggested various barriers to implementing these guidelines, including a lack of training and knowledge among clinicians regarding the efficacy, dosing, and timing of nonpharmacological interventions [22, 30]. Nonpharmacological strategies are also considered to be more time-consuming compared to psychotropic medication. Furthermore, there are only limited evidence-based interventions suitable for patients with early-stage dementia and their caregivers given the focus of previous research on institutionalized patients with severe dementia [31]. To overcome these barriers, there is a need for a tool that translates the current guidelines into clinical practice and integrates a comprehensive assessment into the standard work-up at memory clinics in order to improve early recognition and tailored treatment of NPS in AD.

Recently, a multidisciplinary expert panel proposed such a tool that integrates current models and theories on the causes of NPS to structure the assessment and management of these symptoms following four steps: Describe, Investigate, Create, Evaluate—i.e., the DICE method [10]. This framework identifies NPS, examines possible underlying causes, and consequently integrates pharmacological and nonpharmacological interventions to treat these symptoms following a PCC approach.

Similar approaches to the DICE method have been developed to address NPS in dementia (e.g., “Grip on Challenging Behaviour” [32], “4D Approach” [33], “Act in Case of Depression” [34], “STA OP!”) [35]. However, studies in community-dwelling patients are lacking, as the majority of these methods have been carried out in the nursing home setting. A recent pilot study showed that the use of the DICE method reduced caregiver distress in caregivers of community-dwelling patients with dementia [36] and supports the use of this approach in the outpatient setting. Moreover, the DICE method has been suggested as the most promising nonpharmacological approach to manage NPS in dementia [37]. Besides the evidence on its effectiveness, demonstrating the cost-effectiveness of the DICE method is crucial before this approach can be part of the standard care [18, 38].

The BEhavioral symptoms in Alzheimer’s disease Towards early Identification and Treatment (BEAT-IT) study is developed to increase our understanding of NPS across the spectrum of AD. This project aims to (1) investigate the etiology of the behavioral variant of AD (bvAD) [39] as a model of the neurobiological mechanisms of NPS in AD and (2) study the effectiveness of the DICE method for the management of NPS in patients with MCI and AD. This paper describes the protocol of an intervention study that focuses on the latter aim.

### Objectives

The aim of this study is to use the DICE method to structure and standardize the recognition of NPS in AD in the memory clinic, implement current guidelines for the treatment of NPS in MCI and AD, and to investigate the effects of the treatment on QoL. Note that we will not evaluate the treatments itself (e.g., the efficacy of psychosocial interventions or antidepressants) since those are already evidence-based interventions recommended by current guidelines, but rather examine the benefits of structuring these interventions in the context of the memory clinic. We will do this by investigating the effectiveness and cost-effectiveness of the DICE method in community-dwelling patients with AD or MCI visiting the memory clinic and compare this group to a control group who will receive care as usual (CAU). We hypothesize that the structuring and standardization of the care of NPS with the use of the DICE approach will improve the QoL of both caregivers and patients at the early stages of AD. In addition, implementing the DICE method is expected to allow early recognition of NPS and reduce NPS, caregiver burden, and psychotropic drug use, and is aimed to be cost-effective. By doing so, this study may contribute to the improvement of early identification and management of NPS in AD in memory clinics.

## Methods

The Standard Protocol Items: Recommendations for Interventions Trials (SPIRIT) guidelines were followed for this protocol [40].

### Study design

This study is a prospective multicenter study with a quasi-experimental design (see Fig. 1). In the first part of the study, a control group will be recruited who will receive CAU. After 1 year, we will enroll the second wave of participants who will receive a structured and standardized assessment and treatment of NPS based on the principles of the DICE method. Hence, the enrollment of the control group will be completed before the start of the inclusion of the intervention group. This design has the advantage that it reduces the risk of contamination and crossover between the two groups. Moreover, a crossover design is not possible given the progressive nature of AD. Furthermore, cluster randomization of hospitals is not feasible because of the differences in CAU between the sites. Since patients of both waves will be enrolled in the same sites, we assume that the waves will not show meaningful differences in demographic and clinical characteristics. Also, no substantial changes are expected in the upcoming years regarding current CAU in the memory clinics based on the view of collaborating experts and the organization of care in the last years.

**Fig. 1 Fig1:**
[figure not shown]
Design of the BEAT-IT study. Note that only the assessments are depicted since intervention visits will vary across subjects in the intervention group due to the personalized approach

Subjects will be followed for 6 months while undergoing three assessments during this period. The primary outcome will be the QoL of patients and their caregivers. Secondary outcomes include changes in the prevalence and severity of NPS, caregiver burden, caregivers’ confidence managing NPS, psychotropic medication use, the experiences of patients and caregivers who underwent the DICE method, and the cost-effectiveness of the intervention.

### Eligibility criteria

In order to be eligible to participate in this study, patients must meet all of the following criteria (see Table 1): (a) a clinical diagnosis of probable AD (NIA-AA criteria by McKhann et al. [41]) or MCI due to AD (NIA-AA criteria by Albert et al. [42]) with at least intermediate probability of AD etiology based on: patient history, neuropsychological assessment [43], and neuroimaging (magnetic resonance imaging (MRI) or positron-emission tomography (PET)). The clinical diagnosis needs to be established within the last 2 years so that patients with a diagnosis who visit the memory clinic for clinical follow-up might also participate; (b) presence of NPS established with the Neuropsychiatric Inventory Questionnaire (NPI-Q, presence of ≥ 1 symptoms) administered within the last month [44]; (c) a Mini-Mental State Examination (MMSE) score > 15 so that patients are able to reflect on their QoL [45]; (d) patients need to be community-dwelling; and (e) availability of a reliable informant who is considered to be the primary caregiver.

**Table 1 Tab1:** Eligibility criteria

Inclusion criteria	Exclusion criteria
Diagnosis of MCI due to AD or AD dementia based on patient history, neuropsychological assessment, and neuroimaging within the last 2 years	Meeting the additional criteria of a non-AD neurodegenerative disease (vascular co-pathology is permitted)
Presence of NPS; ≥ 1 symptoms on NPI-Q	Legally incapable to give informed consent
MMSE score > 15	Evidence of current delirium or previous delirium
Patients need to be community-dwelling	Primary (premorbid) psychiatric disorders that could better explain the manifestation of NPS
Availability of a reliable informant	Participating in a clinical (medication) trial

*MCI* mild cognitive impairment, *AD* Alzheimer’s disease, *NPS* neuropsychiatric symptoms, *NPI-Q* Neuropsychiatric Inventory Questionnaire, *MMSE* Mini-Mental State Examination

A potential subject who meets any of the following criteria will be excluded from participation in this study: (a) patients meet the (additional) criteria of any non-AD neurodegenerative disease, except vascular co-pathology; (b) legally incapable (as judged by the attending physician and therefore unable to give a written consent; (c) evidence of current delirium or previous delirium in the past 6 months; (d) primary (premorbid) psychiatric disorders such as schizophrenia or bipolar disorder that could better explain the manifestation of NPS, or current abuse of alcohol or drugs; and (e) currently participating in a clinical trial. Patients are allowed to be on medication (e.g., acetylcholinesterase inhibitors or psychotropic drugs) prior to inclusion since no differences between the two waves are expected regarding the medication use at baseline, and this will be carefully documented in a case report form (CRF).

### Recruitment

Patients will be recruited from six different memory clinics in and around Rotterdam in the Netherlands (Erasmus University Medical Center, Franciscus Gasthuis & Vlietland, Het Van Weel-Bethesda Ziekenhuis, Maasstad Hospital, and Spijkenisse Medical Center) to facilitate patient enrollment and guarantee a good mixture of patients from both academic and general hospitals.

After a diagnosis of MCI or AD dementia is established at one of the memory clinics, study eligibility will be evaluated based on the in- and exclusion criteria by the local attending physician. Alternatively, patients already diagnosed with MCI or AD dementia who visit the memory clinic for clinical follow-up will also be identified based on these criteria.

### Interventions

#### Control group

Participants in the control group will receive CAU at their local hospital. We expect that the CAU will be quite heterogeneous over sites and may consist of psychoeducation about dementia by a nurse or consultant specialized in dementia, the prescription of psychotropic drugs, and/or the referral to a psychiatric outpatient clinic for specialized treatment in patients with severe NPS [46]. Because of these differences, we will carefully keep track of the procedures undertaken by clinicians for patients in the CAU group. Based on recommendations for assessing usual care in clinical trial [47], we will develop a study-specific CRF that will be filled out at the time of enrolment and will be updated at each follow-up visit.

The steps of the DICE method are depicted in Fig. 2. More detailed information on the development and background of the DICE method can be found elsewhere [10]. During the first visit, the patient and caregiver will undergo a consultation by an experienced psychiatrist to establish clinically relevant NPS (*Describe*). Factors related to the patient, caregiver, and environment will be examined following the DICE method [22, 48] and the DICE manual [49]. For factors related to the patient, we will record the chronic somatic conditions using the Cumulative Illness Rating Scale for Geriatrics (CIRS-G) [50] semi-structured interview, followed by a clinical examination to explore the medication changes, pain, sleep hygiene, and sensory changes. If necessary, a lab evaluation will be conducted to screen for infections, thyroid problems, and metabolic disorders. Other patient-related factors including unmet needs, boredom, and emotional well-being will be assessed using the Checklist of Factors to Consider to Identify Potential Causes of Behavioral Symptoms developed by Gitlin et al. [48]. Caregiver-related factors will be screened by using the Relationship Closeness Scale [51], Center for Epidemiologic Studies Depression Scale [52], and the CareQol-7D [53]. This will be extended by history taking on family and cultural expectations, knowledge about dementia, and the availability of support. Environmental factors will be assessed to the patient and caregiver by the Informal Assessment: Brief Questions to Guide Describing Behavioral Symptoms [48]. A full and accurate description of specific behavior will provide more insight about the “who, when, where, and what” about the situations in which the behavior is occurring, while taking safety risks and the level of physical and social stimulation into account (*Investigate*). Thereafter, a multidisciplinary meeting will take place in which a personalized treatment advice is formulated based on the current guidelines on the diagnosis and assessment of NPS in dementia (*Create*) [24–26]. During the second visit, this treatment advice is discussed and adjusted to the needs, values, and characteristics of the patient and caregiver following a PCC approach. Given the large heterogeneity in symptoms, interventions will vary for each individual and can include psychoeducation, psychosocial interventions, caregiver support, and/or pharmacological treatment based on the current (inter)national guidelines [24–26, 54–56]. Notably, the interventions and strategies that will be used to reduce NPS and enhance the QoL are all evidence-based treatment strategies that are or should be carried out in the current clinical practice. Finally, we will monitor treatment progression 1 month after the last visit by telephone (*Evaluate*). Patients and their caregivers are then invited for an extra visit if necessary. In such cases, alternative interventions will be discussed if planned interventions were not implemented or effective. Additional diagnostic procedures or interventions will be monitored in the CRF.

**Fig. 2 Fig2:**
[figure not shown]
The DICE method with examples of questions and actions. Adapted from Kales et al. [10] and Gitlin et al. [48]

### Outcome measures

For the control group, measurements will take place at baseline (T0), with follow-up testing at 3 months (T1) and 6 months (T2). For the intervention group, measurements will take place at baseline (T0), directly after treatment (T1), and follow-up at 6 months (T2). The T1 measurements will be planned after finishing the (psychosocial) intervention and/or when medication is stabilized and thus may vary between subjects in the intervention group. We will gather all relevant clinical and intervention-related information which enables us to study post hoc whether this variation in T1 assessments may have resulted in bias. All measurements will take place at the local hospitals or at the patients’ homes, see Table 2 for an overview of all outcome measures.

**Table 2 Tab2:** Outcome measures

Outcome	Measure	Purpose	Respondent	Time of assessment
Demographic characteristics	For example, age, education, sex, ethnicity, relation to caregiver	Descriptive, covariate, moderator	Patient and caregiver	T0
Clinical characteristics	For example, diagnosis, AD biomarkers, disease duration	Descriptive, moderator	Patient and caregiver	T0*
Disease severity	CDR [57]	Descriptive, moderator	Patient	T0*, T2
Cognitive status	MMSE [58]	Descriptive, moderator	Patient	T0*, T2
Cognitive functioning	Standardized cognitive test battery [43]: RAVLT [59], VAT [60], DS [61], VF [62], LDST [63], SCWT [64], TMT [65]	Descriptive, moderator	Patient	T0*
Functional abilities	A-IADL-Q [66]	Descriptive, moderator	Caregiver	T0, T2
Psychotropic medications	Brown bag review [20]	Descriptive, secondary outcome	Caregiver	T0, T1, T2
Comorbidities	CIRS-G [50]	Descriptive	Patient	T0, T2
Quality of life patient	QoL-AD [67]	Primary outcome	Patient and caregiver	T0, T1, T2
Quality of life caregiver	CarerQol-7D [53]	Primary outcome	Caregiver	T0, T1, T2
Caregiver burden	Perseverance time [68]	Secondary outcome	Caregiver	T0, T1, T2
Caregiver competence managing NPS	Additional NPI-Q item [69]	Secondary outcome	Caregiver	T0, T1, T2
Cost-effectiveness	EQ-5D-5 L [70], ICECAP-O [71] iMTA iVICQ [72], iMTA MCQ [73]	Secondary outcome	Patient Caregiver	T0, T1, T2
NPS prevalence, severity, and distress	NPI-Q [44]	Secondary outcome	Caregiver	T0*, T1, T2
If NPI-Q frequency score ≥ 1 on:				
“Agitation,” “motor disturbances,” “irritability,” “disinhibition”	Cohen-Mansfield Agitation Inventory [74]	Secondary outcome	Caregiver	T0, T1, T2
“Apathy”	Apathy Evaluation Scale-I [75]	Secondary outcome	Caregiver	T0, T1, T2
“Depression,” “anxiety,” “elation”	CSDD [76], RAID [77]	Secondary outcome	Caregiver	T0, T1, T2
“Hallucinations,” “delusions”	BEHAVE-AD subscales psychosis, delusions [78]	Secondary outcome	Caregiver	T0, T1, T2
“Nighttime behaviors”	Sleep Disorder Inventory [79]	Secondary outcome	Caregiver	T0, T1, T2

*AD* Alzheimer’s disease, *CDR* Clinical Dementia Rating, *RAVLT* Rey Auditory Verbal Learning Test, *VAT* Visual Association Test, *DS* Digit Span, *VF* Verbal Fluency (animals), *LDST* Letter Digit Substitution Test, *SCWT* Stroop Color Word Test, *TMT* Trail Making Test, *MMSE* Mini-Mental State Examination, *A-IADL-Q* Amsterdam Instrumental Activity of Daily Living Questionnaire, *CIRS-G* Cumulative Illness Rating Scale for Geriatrics, *QoL-AD* Quality of Life in Alzheimer’s Disease, *iMTA iVIQ* iMTA Valuation of Informal Care Questionnaire, *iMTA MCQ* iMTA Medical Costs Questionnaire, *NPI-Q* Neuropsychiatric Inventory Questionnaire, *CSDD* Cornell Scale for Depression in Dementia, *RAID* Rating Anxiety In Dementia, *BEHAVE-AD* Behavioral Pathology in Alzheimer’s Disease Rating Scale

*Will be carried out during the diagnostic procedure at local hospitals

#### Primary outcomes

The QoL of the patient will be measured by the Quality of Life in Alzheimer’s Disease (QoL-AD) questionnaire [67]. This is one of the most widely used QoL questionnaires in AD and has good psychometric properties [80]. Patients are questioned via a 13-item interview format. The proxy version of the QoL-AD is also used and filled out by the caregiver since previous studies have shown that the caregivers’ perspective on the patients’ QoL might be a more valid indicator of treatment success [81].

The CarerQol-7D will be used to measure the care-related QoL in caregivers [53]. The instrument includes six burden dimensions and a subjective valuation scale for happiness.

#### Secondary outcomes

Changes in NPS will be assessed with the NPI-Q [44], a general screening questionnaire including 12 distinct NPS. For each item, caregivers have to indicate the presence, the severity, and the extent of emotional distress that each symptom causes. Similar to Gitlin et al. [69], we will add a frequency score and will ask caregivers how confident they are in managing a certain symptom on a 5-point Likert scale (0 = not confident to 4 = extremely confident).

A two-step approach will be used to further assess NPS: if certain symptoms are present, as indicated by an NPI-Q frequency score ≥ 1, specific questionnaires will be used to assess these symptoms in more detail. All instruments will be administered to the caregiver. To measure the depressive symptoms, the Dutch version of the Cornell Scale for Depression in Dementia (CSDD) will be used [76]. The CSSD consists of 19 items covering mood, behavioral changes, and circadian changes related to depression and is validated in patients with dementia [76]. Anxiety symptoms will be measured by the Rating Anxiety in Dementia (RAID) scale, an 18-item inventory that includes specific fears and somatic symptoms related to anxiety [77]. Agitation, irritability, aggression, and motor disturbances will be measured by the Dutch version of the Cohen-Mansfield Agitation Inventory (CMAI-D) [82]. Hallucinations will be assessed by the subscale B of the Behavioral Pathology in Alzheimer’s Disease Rating Scale (BEHAVE-AD) [78], and delusions will be assessed by the subscale A of the BEHAVE-AD. Apathy is assessed with the informant-reported Apathy Evaluation Scale (AES-I) [75] and comprises of 18 items. Sleep disturbances will be measured by the 8-item Sleep Disorder Inventory (SDI) [79], an expanded version of the sleep disturbances item of the NPI. Similar to the NPI, caregivers have to score each symptom of the SDI on frequency, severity, and caregiver distress.

Caregiver burden will be measured with the perseverance time, a one-item questionnaire that assesses caregiver burden by asking the period of time (in months) that the informal caregiver thinks he or she is able to maintain the care if the current situation remains stable [68]. This questionnaire is a good predictor for institutionalization [83].

The Clinical Dementia Rating Scale (CDR), MMSE, and a neuropsychological assessment will be administered during the diagnostic procedure at the local memory clinic prior to inclusion. The CDR includes six domains covering cognitive function and IADL associated with dementia [57]. Disease severity will be determined based on clinical diagnosis and CDR global score with MCI due to AD (CDR score 0.5), mild AD dementia (CDR score 1), and moderate to severe AD dementia (CDR score 2–3). Global cognitive function will be measured with the MMSE [58]. The neuropsychological assessment will be carried out according to the Dutch Parelsnoer Institute for Neurodegenerative Diseases [40] and covers the major cognitive domains including memory, attention, processing speed, language, visuospatial abilities, and executive functioning.

The Amsterdam Instrumental Activities of Daily Living Questionnaire (A-IADL-Q) is a proxy measure to detect problems in IADL in patients with dementia [66]. This tool is a reliable and valid instrument to detect changes in IADL over time.

Physical health and comorbidities of the patient will be assessed using the CIRS-G [50]. The severity of 14 common medical problems in the geriatric population (e.g., heart, liver, vascular diseases) will be judged by one of the researchers during a short interview with the patient and caregiver.

Psychotropic medication use will be documented in the CRF. The total number of medications used will be registered and classified according to the ATC coding: antidepressants, antipsychotics, hypnotics and sedatives, anxiolytics, and anti-dementia medications [20].

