### Statistical methods

*T*-tests or chi-square tests will be used to identify the differences in baseline characteristics (e.g., age, education level, disease severity) between the control group and the intervention group. For the primary and secondary study outcomes, we will use an intention-to-treat approach including all subjects irrespective of the adherence to our intervention [89]. Thereafter, we will perform per-protocol analyses with only the subjects who completed the intervention (underwent all DICE steps). We will correct for multiple testing.

We will use the Little’s Missing Completely at Random Test to examine whether the data are missing at random or missing completely at random. The mixed model analyses will be able to handle the data when the missing data is completely at random. Multiple imputation will be used in cases when data is missing at random.

Linear mixed models will be used for the primary and secondary outcomes for the T0, T1, and T2 time points. These statistics are preferred when using longitudinal data because of its advantage in handling missing data and its capacity to deal with nested data and variance in follow-up duration between and within the groups. Changes in the trajectories of the primary and secondary outcomes are compared between the two groups. Subject, hospital, and time are considered as random effects, and baseline measure, group, and disease severity are accounted as fixed effects.

We will perform a cost-utility analysis of the intervention group versus the control group in accordance with the Dutch guidelines for economic evaluations on the basis of questionnaires [90].

Quality and length of life will be combined into quality-adjusted life years (QALYs) using a Markov model to extrapolate lifetime outcomes based on the data from this study combined with literature data. The EQ-5D-5 L, ICECAP-O, and CarerQol-7D data will be transformed into QALYs for patients and caregivers (well-being years for ICECAP-O), using published tariffs obtained from general reference populations [90, 91].

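### The symptom-specific scales depend on NPI-Q symptom presence with no rule for follow-up, so a patient whose symptom resolves may have no follow-up score on that scale

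*Protocol article*

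**What the plan says.** Under Secondary outcomes, symptoms are assessed in two steps: "if certain symptoms are present, as indicated by an NPI-Q frequency score ≥ 1, specific questionnaires will be used to assess these symptoms". Table 2 (Outcome measures) repeats the condition as a sub-heading, "If NPI-Q frequency score ≥ 1 on", above the CMAI, AES-I, CSDD/RAID, BEHAVE-AD subscales and SDI. Each is listed as a secondary outcome at T0, T1 and T2. Neither place says at which visit the condition is judged, whether a triggered scale continues, or what score applies when a scale is not given.

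The general symptom measure has no such condition: "Changes in NPS will be assessed with the NPI-Q", and for each item "caregivers have to indicate the presence, the severity, and the extent of emotional distress that each symptom causes". The Abstract gives the primary endpoint: "Primary outcomes are the quality of life of patients and their caregivers". The quality-of-life instruments are also unconditional in Table 2.

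On analysis, Statistical methods states: "Linear mixed models will be used for the primary and secondary outcomes for the T0, T1, and T2 time points". It adds that "baseline measure, group, and disease severity are accounted as fixed effects". The missing-data plan relies on Little's test, then the mixed model if data are missing completely at random, and multiple imputation if missing at random.

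**The concern.** Whether a scale is given depends on the symptom that it measures. If the condition is reapplied at T1 and T2, a patient whose apathy disappears has no AES-I score at that visit, and the score is absent because the patient improved. Those who improve most leave the comparison, and more of them leave from the arm that works better.

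The planned handling of missing data does not repair this. The missingness depends on the current symptom state, so the mixed model on observed scores is not protected. Imputation that uses the NPI-Q has no observed score on the scale when all its trigger items are zero, so it must extrapolate into an empty stratum.

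The reverse case also has a gap. A symptom that first appears after T0 has no T0 score on its scale, so the baseline covariate is undefined for that patient.

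At stake are the detailed symptom scales, which are the secondary evidence on which symptoms DICE changes and by how much. Scores that are never collected cannot be recovered by a later analysis plan.

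**Working it through.** **Plan figures.** The protocol gives no calculation for these scales. Its only design figure, N = 86 for the between-group comparison, concerns quality of life. It reproduces with f = 0.25, three measurements and correlation 0.5 (f and the correlation are assumed), but does not bear on this point.

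**Inputs not in the documents.** Resolution rates by arm, the correlation between the NPI-Q frequency rating and the scale, and the correlation between visits are not given. All are assumed below and varied.

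**Case 1: DICE acts only by full resolution.** Let a resolved patient score 0, let an unresolved patient average 10 in both arms, and let 20% resolve under usual care and 40% under DICE.
- All patients scored: 0.6 × 10 − 0.8 × 10 = 6 − 8 = −2.
- Only still-symptomatic patients scored: 10 − 10 = 0.

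None of the effect is retained, whatever the two resolution rates.

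**Case 2: DICE shifts severity in everyone.** In model A, the latent severity has T0-T2 correlation 0.6, the true effect is −0.5 SD, and 30-50% of patients have the symptom at T0. The scale is the latent value plus noise of 0.3 SD. The follow-up score is deleted when the NPI-Q condition fails. Model B takes patients symptomatic at T0, a correlation of 0.5 between visits, resolution of 10-30% under usual care and 20-50% under DICE, and sets the shift to match those rates. Both compare the baseline-adjusted group difference among patients still scored with that from complete data.

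| Correlation of NPI-Q condition with severity | Retained, model A | Retained, model B |
|---|---|---|
| 1.0 | 38-47% | 50-71% |
| 0.9 | 52-58% | 61-77% |
| 0.7 | 74-77% | 77-86% |
| 0.5 | 86-90% | 89-93% |

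At correlation 1.0 in model A, the symptom persists in 58-71% of T0-positive controls and 35-49% of T0-positive DICE patients. The difference among those still scored is about −0.19 to −0.23 SD instead of −0.5 SD.

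**Which scales are most exposed.** By Table 2, any of four NPI-Q items triggers the CMAI, any of three triggers the CSDD/RAID pair, and either of two triggers the BEHAVE-AD subscales. One item alone triggers the AES-I and one alone the SDI, so for these the score is lost as soon as that item resolves.

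**Check on a tempting repair.** Controls are enrolled first, so any skipped scales will sit mainly in the control wave. Suppose skipped controls receive the scale minimum (taken as the 2nd percentile of all baseline scores) while resolved DICE patients are actually measured. In model A at correlation 1.0 the estimate moves from about −0.5 SD to between −0.02 and +0.37 SD. The benefit is erased or reversed, which is worse than the attenuation being repaired.

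**The case against.** The strongest reply is that the text never says the condition is reapplied at each visit. Listing each scale at T0, T1 and T2 also fits a condition judged once at T0, followed by two repeats. On that reading the bias disappears for T0-positive patients, and the CRF instructions may already say so. This stands as a limit on the claim. It does not remove the ambiguity, because the NPI-Q is itself repeated at every visit and a data collector following the article could reasonably skip the scale.

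A reader might infer that the benefit of DICE as a whole would be largely hidden. The documents do not support that. The QoL-AD, CarerQol-7D and NPI-Q are collected at all three visits without the condition, and the NPI-Q records that a symptom has gone. The hypothesis that DICE reduces symptoms can be tested there.

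A reader might also take the loss to exceed half of the effect. That needs the frequency rating and the scale to share essentially one latent variable, or DICE to act mainly by full resolution. Neither is documented, and a single caregiver rating is unlikely to track a multi-item scale perfectly.

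Finally, one might extend the point to the caregiver-confidence item. The text says only that the researchers "will ask caregivers how confident they are in managing a certain symptom on a 5-point Likert scale". It does not restrict the question to symptoms present at that visit, so the extension is not established.

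**Conclusion.** The concern holds in a limited form. The protocol makes five groups of secondary scales conditional on the symptom they measure and leaves the follow-up rule open. If the condition is reapplied at each visit and DICE resolves more symptoms than usual care, the group difference on these scales is biased toward zero. The planned model and imputation do not correct this. A symptom arising after T0 has no baseline value in either reading.

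Roughly 40-90% of the effect is retained under the assumed severity-shift models, and none under resolution alone. These figures rest on assumed resolution rates and correlations. The direction is firmer than the size, and it depends on more resolution under DICE. The primary outcomes and the NPI-Q are not affected. The point still deserves action because data not collected are lost and the change is small.

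**What to change.** 1. State that a scale triggered at T0 is given at T1 and T2 whatever the NPI-Q then shows. If the condition was always meant to be fixed at T0, say so explicitly.
2. Define each scale's analysis set as the patients who are positive for its trigger at T0.
3. Report symptoms arising after T0 through the NPI-Q, which has a T0 value for everyone.
4. If some control follow-up scales have already been skipped, do not impute the scale minimum in controls only. In the main comparison, handle follow-up visits where the symptom is absent identically in both waves, for example by ranking symptom absent as the best category in both groups. Use the measured scores of resolved patients in a sensitivity analysis.

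The cost is one line in the CRF instructions and a few more caregiver questionnaires per follow-up visit. If the common ranking rule is needed, the main result for these scales becomes an ordinal comparison and no longer a mean difference in points. The article reports control recruitment as still under way and the intervention wave as not yet started, so the collection rule can be in place for all DICE patients.
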